#### Participants

##### Patients

Older adults presenting to surgical clinics will be screened for eligibility criteria by study staff. Eligible participants are patients aged ≥85 years or those aged ≥65 years with multiple comorbid conditions (>2), diagnosed or suspected cognitive impairment, diagnosed or suspected functional impairment, or poor nutrition (documented weight loss of 10% within a year). The inclusion criterion is eligible older adults planning to undergo elective major abdominal surgery. Exclusion criteria are non-English speakers (because we lack resources for translation) or the absence of a caregiver for those without decisional capacity.

##### Health Care Professionals

Consistent with implementation research, health care professionals using the pCGA implementation package are considered study participants [76]. As participants from among the health care professionals who participated in the co-design will be recruited for the pilot trial, they will be familiar with the intervention. Surgeons referring patients from the 2 clinics (n=12) and health care professionals engaged at the pCGA clinic (n=10) will be asked to participate in the pilot.

##### Recruitment and Enrollment

Clinic staff will approach potential participants to determine interest, and a study team member will then share study details and obtain consent. At baseline, 40 patients per year are seen for pCGA. We expect to enroll 20 patients over the pilot period. All patient data for the pilot will be obtained via chart abstraction. The study will be subject to IRB approval.

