### Phase 3: Pilot Trial of the pCGA Implementation Package

#### Study Design

We will conduct a pretest-posttest pilot study of the implementation package over 10 months, conducted at the clinic level at 2 busy academic medical center surgical subspecialty clinics performing major abdominal surgery (selecting one that does not routinely refer for pCGA in addition to one that does routinely refer). We will collect baseline prepilot data via retrospective chart abstraction from the year before the intervention. After an implementation rollout period of 2 months, postintervention data will be collected over 10 months. Specifically, we will assess outcomes according to the RE-AIM framework [38], using chart abstraction for patient-level data and simple self-reported surveys for the health care professionals. We hypothesize that a user-designed implementation package will improve the reach and adoption of the pCGA compared to the historic baseline.

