The pilot trial will test the pCGA implementation package using a pretest-posttest design at 2 surgical clinics enrolling 20 patients in the preimplementation period and 40 in the postimplementation period. Using the RE-AIM framework [38] we will measure reach, effectiveness, adoption, implementation, and maintenance. We aim to improve reach and maintain fidelity. Exploratory analyses will assess differences across traditionally underrepresented groups [69] (rural vs urban, racial majority vs minority groups, men vs women vs other gender identities, and Hispanic vs non-Hispanic ethnicity). We hypothesize that reach will increase while maintaining fidelity in the postimplementation phase of the pilot.

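### The article gives two irreconcilable patient numbers for the Phase 3 pilot: 20 over the pilot period, or 20 before plus 40 after implementation

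*Protocol article*

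**What the plan says.** Three parts of the protocol article bear on the size of the Phase 3 pilot.

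- **Recruitment and Enrollment (Phase 3 Methods)** gives a baseline volume and an expected enrolment: "At baseline, 40 patients per year are seen for pCGA. We expect to enroll 20 patients over the pilot period". The same paragraph says that a study team member obtains consent.
- **Results, Phase 3** gives a different account of the same pilot: "enrolling 20 patients in the preimplementation period and 40 in the postimplementation period".
- **Study Design (Phase 3 Methods)** sets the windows. The pilot is described as "We will conduct a pretest-posttest pilot study of the implementation package over 10 months". The pre-period is retrospective: "We will collect baseline prepilot data via retrospective chart abstraction from the year before the intervention". For the post-period, "After an implementation rollout period of 2 months, postintervention data will be collected over 10 months". Two surgical clinics take part, "selecting one that does not routinely refer for pCGA in addition to one that does routinely refer".

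The article does not say which clinics the 40 per year covers, and it gives no consent rate.

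**The concern.** A reader who takes the patient number from the Methods plans for a different study from one who takes it from the Results. The prospective sample is either 20 or 40, a factor of two, and nothing in the article says which figure governs.

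The Data Analysis section disclaims a formal power calculation, so no power claim is at stake. It does say that the pilot is meant to yield preliminary point estimates and confidence intervals for planning a later trial. The number of patients per period decides how much information those estimates will carry, so it should be stated once and consistently.

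The baseline figure of 40 per year, printed directly beside the expected 20, might be expected to show which number is right. It does not, because its scope is undefined and it counts patients seen rather than patients enrolled.

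**Working it through.** **Inputs, all from the article**

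- Baseline volume: 40 pCGA patients per year (Recruitment and Enrollment).
- Enrolment, Methods: 20 over the pilot period (Recruitment and Enrollment).
- Enrolment, Results: 20 pre and 40 post (Results, Phase 3).
- Pre-period: one year of charts. Post-period: 10 months after a 2-month rollout (Study Design).

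**Step 1. Can the two enrolment statements be reconciled?**

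| Reading of pilot period | Methods | Results | Agree? |
|---|---|---|---|
| Prospective (post) period only | 20 | 40 | No |
| Whole pilot, pre and post | 20 | 20 + 40 = 60 | No |

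The first reading is the more natural one, because the pre-period is retrospective chart data. The conflict remains on either reading.

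**Step 2. Does the baseline rate pick out one of the figures?**

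Patients expected at an unchanged rate = 40 × months / 12.

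- Baseline year: 40 × 12/12 = 40.
- 10-month post window: 40 × 10/12 = 33.3.
- 12 months, if rollout is counted (2 + 10; the staff surveys are also timed at 6 and 12 months into the pilot): 40.

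Comparison with the printed figures:

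- 20 in 10 months: 20/33.3 = 0.60, or 40% below the baseline rate (20 × 12/10 = 24 per year).
- 20 in 12 months: 20/40 = 0.50, or 50% below.
- 40 in 10 months: 40/33.3 = 1.20, or 20% above (40 × 12/10 = 48 per year).
- 40 in 12 months: equal to the baseline rate.
- 20 in the pre-period year: half of the 40 expected at the baseline rate.

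So at face value the baseline rate reproduces neither the 20 over 10 months nor the 20 in the baseline year.

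**Step 3. How far does that depend on what the 40 per year counts?**

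Let *f* be the share of enrolled patients among those counted in the 40 per year, combining clinic scope and consent. The article gives no value, so a range is assumed. The number seen that corresponds to 20 enrolled is 20/*f*, compared with 33.3 over 10 months.

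| *f* (assumed) | Seen in 10 months | Against 33.3 |
|---|---|---|
| 1.00 | 20.0 | 40% below |
| 0.75 | 26.7 | 20% below |
| 0.60 | 33.3 | equal |
| 0.50 | 40.0 | 20% above |

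Depending on *f*, the same 20 enrolled patients can go with a fall, no change or a rise in pCGA volume. The baseline figure therefore cannot decide between the two enrolment statements.

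**The case against.** The strongest defence is that 20 enrolled and 40 seen per year are different quantities. Enrolment requires consent, and the 40 may describe the whole pCGA service. Phase 1 plans to interview referring surgeons from a range of specialties, and one of the two pilot clinics does not routinely refer. On that view, 20 baseline patients from the two clinics fits a service-wide 40 per year, and 20 enrolled need not mean fewer patients seen. This is right as far as it goes. It removes any firm conclusion from the baseline rate, but it does not reconcile 20 with 40, or 20 with 60.

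Several stronger readings are tempting, and the article does not support them:

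- **That the plan forecasts a 40% fall in pCGA volume, against its own hypothesis.** This needs the 40 per year to be the two clinics' volume and every patient seen to be enrolled. Neither is stated.
- **That the 20 and the 40 were swapped between periods.** This is possible, but nothing in the article confirms it.
- **That the expected rise is built in as a quota.** The Methods state an expectation. If the pre-period is the full year, the Results figures amount to a 2.4-fold rise in monthly rate, (40/10)/(20/12). That is in the hypothesised direction and is not in itself an error.
- **That enrolled patients serve as the denominator for reach.** Table 2 defines reach as referred over potentially eligible patients, so they do not. For the same reason, confidence intervals computed on 20 or 40 patients would not describe the precision of reach.

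It is also true that an article may leave detailed accrual forecasts to the full protocol. That does not excuse two printed figures that disagree.

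**Conclusion.** The stated Phase 3 patient number is wrong as written. The Methods and the Results give irreconcilable figures: 20 against 40 if the pilot period is the prospective period, 20 against 60 if it is the whole pilot. This part rests on no assumption beyond the printed text.

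The 40% shortfall against the baseline rate (20 against about 33 in 10 months) is conditional. It shows only that the baseline figure does not resolve the conflict while its scope and the consent rate are unstated; it is not evidence of a planned decline. No power or precision statement in the article changes, because none is made.

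**What to change.** 1. Correct Recruitment and Enrollment and the Results text for Phase 3 so that both give the same single number for the pre-period and the same single number for the post-period.
2. State whether the 40 per year refers to the two pilot clinics or to the whole pCGA service. If it is the whole service, give the figure for the two clinics.
3. State whether each count is patients seen for pCGA or patients consented. For the retrospective pre-period, say what enrolment means there, for example the number of charts abstracted. If the post-period count is consented patients, give the assumed consent rate.

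The cost is restated figures and a sentence or two of definition. No extra patients and no change of design are required.

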##### Intervention

The pCGA implementation package (generated via phase 2) will include a set of implementation strategies [74,75] and an explicit stepwise plan defining the people, tasks, tools or technology, relevant organizational factors, and physical or virtual environment [65] for the pCGA. The implementation package will target systems-level processes to promote pCGA administration before surgery (eg, automating referrals in the electronic medical record, improving patient education materials, or increasing telehealth opportunities).

#### Data Collection and Variables

We will obtain quantitative data from two sources: (1) chart abstraction for patients and (2) self-reported survey instruments for health care professionals.

#### Chart Abstraction

Trained research assistants will prospectively abstract and enter data into a deidentified database on a secure server using a data dictionary. We will conduct random audits for interrater reliability according to best practices for retrospective chart review [77]. Patient-level characteristics will include demographics (age, sex, height, weight, zip code, race, and ethnicity), comorbidities (diabetes, chronic corticosteroid use, cancer diagnosis, congestive heart failure, chronic obstructive pulmonary disease, bleeding disorders or anticoagulant use, and renal insufficiency and dialysis). Clinical data from the pCGA will include polypharmacy (anticholinergic burden score [78] and Beers criteria medications [79]), physical function (Timed Up and Go Test [80], Lawton Independent Activities of Daily Living scale [81], and activities of daily living [82]), cognition (Montreal Cognitive Assessment [83]), mood (Patient Health Questionnaire-9 [84]), nutrition (Mini Nutritional Assessment–Short Form [85] and BMI), multiple chronic conditions (Charlson comorbidity index [86,87] and revised cardiac risk index [88]), documentation of code status, completion of health care power of attorney forms, and recommendations for additional tests or referrals (eg, physical therapy). Clinical data from the surgical hospitalization will include the date of surgery, procedure performed, postoperative complications (pneumonia, myocardial infarction, surgical site infection, sepsis, urinary tract infection, venous thromboembolism, renal failure, readmission, and unplanned reoperation), postoperative delirium, the date of discharge, discharge destination, readmission within 30 days, and death. We will abstract postoperative delirium using a validated method [89-91].

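### Abstraction is retrospective at baseline and prospective in the pilot, so ascertainment of delirium and complications may differ by period, in either direction

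*Protocol article*

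**What the plan says.** The phase 3 Study Design section sets the comparison: "We will collect baseline prepilot data via retrospective chart abstraction from the year before the intervention", and then "After an implementation rollout period of 2 months, postintervention data will be collected over 10 months". The Recruitment and Enrollment section makes the chart the only source for patients: "All patient data for the pilot will be obtained via chart abstraction".

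The Chart Abstraction section describes the work: "Trained research assistants will prospectively abstract and enter data into a deidentified database on a secure server using a data dictionary". In one paragraph it lists what is taken from the pCGA visit ("Clinical data from the pCGA will include polypharmacy", followed by function, cognition, mood, nutrition and other items) and what is taken from the admission ("Clinical data from the surgical hospitalization will include the date of surgery, procedure performed, postoperative complications", followed by delirium, discharge, readmission and death). It gives two further safeguards besides training and the data dictionary: "We will conduct random audits for interrater reliability according to best practices for retrospective chart review", and "We will abstract postoperative delirium using a validated method".

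Under Outcomes, reach and adoption are primary and postoperative length of stay is the primary effectiveness outcome. Delirium and the composite of death or complications are exploratory in the text; Table 2 lists 30-day morbidity and mortality as secondary. The Data Analysis section wants preliminary event rates with confidence intervals for planning a later study.

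**The concern.** In a pretest-posttest design the calendar period carries the whole comparison. Anything else that changes with the period is mixed into the result, and here the mode of abstraction changes with it. Delirium, and several of the listed complications, are not simply read off a chart; someone has to decide whether the notes amount to an event. That decision may come out differently when a completed record is read long afterwards than when a chart is worked through as the pilot proceeds. It may also be coloured by what the reader already knows, since the pCGA results and the outcomes belong to one abstraction process.

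At stake are the event rates that are to guide the choice of endpoint for the next trial, and the secondary comparison of 30-day morbidity. A shift in ascertainment moves the point estimates, and the confidence intervals will not show it.

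**Working it through.** The plan gives no figure for this point and disclaims a formal power calculation, so there is nothing to reproduce. The check has two parts.

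**What the text establishes**
- Baseline charts: retrospective (Study Design).
- Pilot charts: prospective (Chart Abstraction). That sentence names no period, but it cannot describe charts from the year before the intervention.
- pCGA findings and outcomes: one list and one process, with no stated separation.
- Table 2 ties fidelity to the record at the pCGA visit and at surgery. In the pilot, some pCGA information is therefore likely to be read before the postoperative outcomes exist.
- Safeguards: the data dictionary and the validated delirium method reduce error in general. The audit measures agreement between raters. Two raters can agree well within each period while both shift between periods, and the article does not say that the audit is balanced by period.

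**Scale, under assumptions**

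Inputs: true event rate p = 25% in both periods, borrowed from the Introduction's average complication rate; sensitivity of coding by period, assumed; specificity assumed equal in both periods; 20 and 40 patients, from the phase 3 part of the Results section.

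Apparent rate = p × sensitivity + (1 − p) × (1 − specificity).

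With specificity 1.00:
- Sensitivity 0.80 against 0.90: 0.25 × 0.80 = 20.0% and 0.25 × 0.90 = 22.5%. Spurious difference 2.5 points.
- Sensitivity 0.70 against 0.90: 0.25 × 0.70 = 17.5% and 22.5%. Spurious difference 5.0 points, a ratio of 22.5/17.5 = 1.29, or 0.78 if the periods are swapped.

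With specificity 0.97 in both periods, each rate rises by 0.75 × 0.03 = 2.25 points and the differences stay at 2.5 and 5.0 points.

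Sampling error of the difference at 25%:
- SE = √[0.25 × 0.75 × (1/20 + 1/40)] = √(0.1875 × 0.075) = 0.1186
- 95% half-width = 1.96 × 0.1186 = 0.232, about 23 points.

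The assumed bias is thus 2.5/11.86 = 0.21 to 5.0/11.86 = 0.42 standard errors. The half-width is the same if the group sizes are 40 and 20. That matters because Recruitment and Enrollment speaks of 40 patients a year at baseline and 20 over the pilot, the reverse of the Results section.

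**The case against.** A reader might infer several stronger things, and the document supports none of them.

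- **That the same assistant codes a patient's pCGA data and outcomes, without masking.** The article is silent on assignment and masking. A condensed article commonly leaves these to the full protocol or an abstraction manual, so the silence is not a fault in itself.
- **That pilot patients are followed live.** All patient data come from the chart, and the audit is modelled on retrospective chart review. Prospective abstraction need mean no more than earlier reading of recorded notes.
- **That the bias works against the package.** Nothing fixes the direction. Closer reading in the pilot could find more events; a team that hopes for benefit could code fewer.
- **That knowledge of pCGA results belongs to the pilot alone.** pCGA was already in use at baseline, and one of the two clinics routinely refers, so some baseline charts hold the same cognition scores.
- **That the damage could not be undone.** Charts persist and could be abstracted again, at extra cost.

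The best argument for leaving the plan alone is proportion. The primary outcomes are referral measures, length of stay is a difference between two dates, the exposed outcomes are secondary or exploratory, and sampling error far exceeds any bias of the size assumed here. This stands, and it limits the severity. It does not remove the point: the difference in mode is stated in the text, it coincides with the comparison, and the stated safeguards do not address it. A larger later trial would reduce sampling error but not a bias carried into its planning figures.

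**Conclusion.** The concern holds in a limited form. The article states different modes of abstraction for the two periods and names no step that makes the coding of delirium and complications comparable between them. Ascertainment may therefore differ by period, in either direction. Differences of 2.5 to 5 points follow if sensitivity differs by 10 to 20 points at a 25% event rate with equal specificity. Those sensitivities are assumptions, and the true size is unknown. Such a shift would not be visible within a half-width of about 23 points, but it would move the event rates used for planning and the secondary 30-day morbidity comparison. Reach, adoption and length of stay are little affected. Severity is low; the case for acting is that the change is cheap.

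**What to change.** Before phase 3 starts:

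1. Keep referral and fidelity abstraction prospective. Table 2 evaluates trends in reach, adoption and implementation at 6 and 12 months, and a single pass over all data at the end would defeat the 6-month reading.
2. Code delirium and complications for both periods by one retrospective procedure, after 30-day follow-up is complete, with charts in random order across periods.
3. Code them from the inpatient record before the pCGA note is opened, and where staffing allows by an assistant who did not abstract that patient's pCGA.
4. Draw the planned interrater audit equally from both periods and report agreement by period.

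This mainly reorders work already planned. The costs are that outcome coding is concentrated at the end of the pilot, and that masking to period stays incomplete because chart dates are visible. If the full protocol or an abstraction manual already provides for this, a sentence saying so would be enough.

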#### Outcomes

The primary outcomes of this pilot trial will be reach and adoption, assessed using the RE-AIM framework [38] (Table 2). Reach refers to the percentage and characteristics of older adults receiving the pCGA intervention, while adoption accounts for those health systems and health care professionals who refer patients for, or deliver, the pCGA [38,92]. Of note, implementation in the RE-AIM framework refers to fidelity, or the extent to which an intervention is delivered as intended. We will expand the implementation domain to include measures of fidelity, as defined by NIH Best Practices [40], as well as feasibility, acceptability, and appropriateness according to the taxonomy of implementation outcomes developed by Proctor et al [93]. The primary effectiveness outcome will be postoperative length of stay, which is an easily measured, continuous outcome variable commonly used in the surgical literature on pCGA [29]. We will collect exploratory measures to inform the selection of effectiveness outcomes for a future implementation-effectiveness trial. These exploratory outcome measures will include (1) a composite of death or postoperative complication events; and (2) data points relevant to the pCGA, including a cognitive outcome (postoperative delirium), functional outcome (discharge destination to home, rehabilitation, or skilled nursing), nutritional outcome (discharge diet, albumin level, and weight at discharge), and polypharmacy (Beers criteria discharge medications [79], anticholinergic burden score [78], and number of opioid pain pills prescribed at discharge).

**Table 2 table2:** The reach, effectiveness, adoption, implementation, and maintenance (RE-AIM) domains and associated outcome measures.

Domain	Definition	Measurement
Reach	The percentage and characteristics of older patients who receive pCGA^a^ before abdominal surgery	Referred ÷ potentially eligible patients Comparison of referred ÷ eligible patients by age, sex, race, ethnicity, BMI, and zip code Target reach: >50% referral of eligible pCGA patients per clinic
Effectiveness	The improvement in clinical outcomes from pCGA receipt	Primary: postoperative length of stay Secondary: 30-day morbidity and mortality (refer to Chart Abstraction section)
Adoption	Surgeon intent, decision, and action to refer eligible patients for pCGA	Percentage of surgeons referring ÷ total surgeons in the pilot clinic Target adoption: >75% of surgeons achieving >50% referrals
Implementation: fidelity	Multifaceted outcome that includes (1) treatment *dose* or amount of intervention delivered, (2) quality or content of intervention delivered by health care professionals, and (3) treatment receipt and enactment by patients (NIH^b^ Best Practices) [40]	(1 and 2) Percentage of completed pCGA components, as abstracted from the medical record at pCGA visit (3) Completion of pCGA recommendations, as abstracted from the medical record at the time of surgery Target fidelity: >90% of pCGA components completed
Implementation: feasibility^c^	Perceived ease of use of pCGA implementation package	Feasibility of intervention measure (4-item survey) [94]
Implementation: acceptability^c^	Satisfaction with the pCGA implementation package	Acceptability of implementation measure (4-item survey) [94]
Implementation: appropriateness^c^	Fit and relevance of pCGA implementation package	Intervention appropriateness measure (4-item survey) [94]
Maintenance	The extent to which pCGA use is sustained over the pilot period	Trends in reach, adoption, and implementation outcomes will be evaluated at 6 months and 12 months

^a^pCGA: preoperative comprehensive geriatric assessment.

^b^NIH: National Institutes of Health.

^c^The feasibility, acceptability, and appropriateness of the pCGA implementation package will be assessed via surveys administered to health care professionals (eg, surgeons, geriatricians, advanced practice providers, nurses, medical assistants, technicians, and staff).

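### The primary outcome reach is defined as receiving the pCGA but is measured and targeted as referral, so its >50% target can be met with fewer than half of eligible patients assessed

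*Protocol article*

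**What the plan says.** The Outcomes section of phase 3 ranks the outcome: "The primary outcomes of this pilot trial will be reach and adoption, assessed using the RE-AIM framework". It then defines it: "Reach refers to the percentage and characteristics of older adults receiving the pCGA intervention". The definition column of Table 2 agrees: "The percentage and characteristics of older patients who receive pCGA", with the qualifier that this happens before abdominal surgery.

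The measurement column of the same row uses a different event:

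- The ratio is "Referred ÷ potentially eligible patients".
- The comparison by age, sex, race, ethnicity, BMI and zip code again has referred patients in the numerator, this time over eligible patients.
- The threshold is "Target reach: >50% referral of eligible pCGA patients per clinic".

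Referral also belongs to the other primary outcome. In the Outcomes text, "adoption accounts for those health systems and health care professionals who refer patients for, or deliver, the pCGA". Table 2 sets "Target adoption: >75% of surgeons achieving >50% referrals".

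**The concern.** The definition and the formula in one table row name different events. The article treats these events as distinct. The research question in the Background section pairs adoption with provider use and reach with patient access. The Predicted pCGA Process Map section has the surgeon place a referral, with the clinic visit following as its own step. The phase 1 interviews ask separately about scheduling and attending.

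Two things are at stake. First, anyone following Table 2 as written will report a referral proportion under the name of reach and judge success against it, although a referred patient may never be assessed. Second, both primary targets rest on the same act, counted per clinic for reach and per surgeon for adoption, so neither counts a patient who was assessed.

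The package may also act on the numerator directly. One example in the Intervention section is "automating referrals in the electronic medical record", which could raise the ratio whether or not a visit follows.

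**Working it through.** **Plan's own figure.** The 50% is a set target. The Data Analysis section says power calculations do not apply, so there is no derived figure to reproduce.

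**Is receipt measured as reach anywhere else?**

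- Fidelity in Table 2 is scored from the record of the pCGA visit, so a referred patient without a visit has nothing to score.
- Maintenance follows trends in the same reach measure.
- The Data Analysis section says only that recruitment data will inform reach.

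No receipt-based ratio is given.

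**Identity.** With one denominator,

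received ÷ eligible = (referred ÷ eligible) × (received ÷ referred).

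If patients reach the pCGA clinic through referral, received ÷ referred is at most 1. The measured ratio is then an upper bound on reach as defined, and the two agree only if every referred patient completes the pCGA before surgery.

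**Inputs.** The 50% threshold comes from Table 2. The article does not give the share of referred patients who complete the pCGA, so it is an assumption, varied here from 50% to 100%. The referral levels of 51%, 60% and 75% are illustrative; all three meet the target.

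Receipt = referral × completion:

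| Referral | 100% | 90% | 80% | 70% | 60% | 50% | Completion needed for receipt >50% |
|---|---|---|---|---|---|---|---|
| 51% | 51.0% | 45.9% | 40.8% | 35.7% | 30.6% | 25.5% | above 0.50/0.51 = 98.0% |
| 60% | 60.0% | 54.0% | 48.0% | 42.0% | 36.0% | 30.0% | above 0.50/0.60 = 83.3% |
| 75% | 75.0% | 67.5% | 60.0% | 52.5% | 45.0% | 37.5% | above 0.50/0.75 = 66.7% |

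A clinic just over the target has almost no room for loss between referral and visit. A clinic well over it has a good deal.

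**Denominator.** The row uses potentially eligible in its ratio and eligible in its subgroup comparison and target. If the potentially eligible group is wider, the first ratio is pulled down, which could offset some of the excess. The target line itself refers to eligible patients, so the table above applies to it directly.

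**The case against.** The strongest reply accepts the mismatch and disputes what can be built on it. Four points stand.

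1. **No extra patient assessed.** A reader might infer that the target could be passed without one more patient receiving the pCGA. That is arithmetically possible: with an assumed 100 eligible patients a year and 40 still seen, 51 referrals meet the target and receipt stays at 40%. But the article does not give the number eligible, and it does not say that the 40 patients seen per year all come from the two pilot clinics. One of those clinics is chosen because it does not routinely refer. If a fair share of its newly referred patients attend, receipt there probably rises. The documents do not support this reading as an expectation.
2. **Met target means receipt below half.** This does not follow either. At 75% referral and 70% completion, receipt is 52.5%.
3. **A trial launched on a false pass.** No go/no-go rule is tied to the 50%. Future Directions makes the next trial depend on successful adaptation of the package, and the Data Analysis section describes the pilot as supplying preliminary estimates.
4. **Automated referral.** It is only an example for a package not yet designed. The same sentence names patient education and telehealth, and the phase 2 strategy examples include travel vouchers. These can act on attendance.

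It can also be said that receipt is not invisible, because pCGA clinical data are abstracted and loss after referral could be seen in them. That is true, but it does not make receipt the stated primary measure. None of these points reconciles the definition with the formula.

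**Conclusion.** The inconsistency is real, lies within one table row, and concerns a primary outcome. As written, the pilot will report referral as reach. The direction of the error is settled under two conditions: a common denominator, and entry to the pCGA through referral. The measured value is then at or above reach as defined, and >50% referral does not establish >50% receipt.

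The size is not known. It depends wholly on the completion rate among referred patients, and the percentages shown are illustrations over an assumed range. The conclusion rests on the contradiction itself and needs no forecast of how many patients would be missed. It should be corrected before the pilot starts. Ethical Considerations states that phase 3 activities await IRB approval, so there is still time.

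**What to change.** In Table 2, Reach row:

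- **Measure.** Reach = patients with a completed pCGA visit in the preoperative period ÷ all eligible patients, per clinic, computed the same way in the baseline and postintervention periods. Define the preoperative period as before surgery or before a decision not to operate. Eligibility is based on planned surgery, so a patient who is assessed and then does not have the operation should still count as reached.
- **Denominator.** Use one term throughout, with one definition, in the ratio, the subgroup comparison and the target.
- **Target.** State it on the receipt measure. Either keep >50% and acknowledge that this is stricter than >50% referral, or restate the figure. That choice is the investigators'; the article gives no basis for a particular value.
- **Referral.** Keep referred ÷ eligible as an adoption or process measure. Shown beside receipt, it locates any loss between referral and visit.

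**Cost.** The Chart Abstraction section already lists pCGA clinical data and the date of surgery. It does not name the date of the pCGA visit, so that field must be confirmed in the data dictionary. The eligible count is already needed for the present ratio. Reported reach will be equal to or lower than the referral figure, and a retained 50% target will be harder to meet.
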